#### Social Presence

Certain specific enhancements have been implemented in study arm 1 in accordance with points made in Mohr’s supportive accountability model [25]. Added social presence aims to give the self-help tool a personal feel, creating a form of alliance between the user and the Web-based self-help tool by replicating that aspect of human support. We aim to recreate rapport similar to what typically is found in client-counselor relationships, without the need to have such a counselor on constant standby. It has been argued by Mohr et al [25] that adherence increases when there is accountability to a coach, who should be seen as trustworthy, benevolent, and having expertise. By introducing a mostly automated eCoach named Deborah, we seek to quite literally give our Web-based tool a face. Although difficult to define one individual who implies the aforementioned attributes to all potential users of the self-help tool, we sought out an eCoach who appears visually friendly and supplemented the representation of benevolence with video scripts and emailed texts that suggest expertise, as well as trustworthiness (see Figure 2).

We created short introduction videos for most of the modules, in which Deborah greets the user, gives her opinion on the importance of certain key points within the module, and finishes by wishing the user an enjoyable time working on the module and acknowledging that they will see each other again in the next module. Additionally, a picture of the eCoach Deborah will be constantly displayed on the dashboard.

She also will personally invite users to write to her should they have any questions or problems. As in the chat version of the first CANreduce study [10], we expect that the number of participants who will actually take her up on this offer will be relatively small. However, we also expect that the assurance that they have the option to write to her will exert a positive impact on their adherence and, thereby, increase their treatment success. Emails written to the eCoach’s address will be answered by available study collaborators—if needed after consultation with a certified therapist; consequently, the answer that querying subjects will receive will address whatever issue or issues they have. In this way, however, the task of replying to emails can be spread out among multiple persons, while retaining that element of personal, one-on-one rapport. It is assumed that the content of this feedback will not, in itself, enhance the effectiveness of the program, but that having the option for direct contact with their own coach will enhance subjects’ perception of the coach’s benevolence and legitimacy.

Furthermore, automatic email reminders or module suggestions will have a greater personal touch in the adherence-focused, guidance-enhanced version with a social presence (Deborah) than in the version without the social presence (no Deborah). In such correspondence, the participants will be addressed by their username; emails and other written communication from the eCoach will be signed as “your eCoach Deborah”; and all text will be written from a first-person perspective (eg, modules will be recommended by her personally; see Textbox 1).

For technical reasons, only one eCoach has been introduced in this newer version of CANreduce. If the demand for personal feedback by the eCoach proves to be greater than expected, replies will be written by multiple coaches. As it could be perceived as deceitful if they all represented themselves as Deborah, the coaches will each sign those emails as an associate or representative of eCoach Deborah.

Therefore, although participants in both active study arms will receive the same level of support, those in the second study arm will be supported by an undisclosed entity, whereas the form of support provided to those in the first study arm will appear to be more intimate and more closely resembling face-to-face coaching.

#### Control Conditions

The control condition will be TAU, as it cannot be ruled out that participants who are allocated to the third study arm will seek out other treatment options during the waiting period. At the last follow-up assessment, participants will be asked if, over the course of their 3 months in the study, they used other treatments and what they were; these data will then be analyzed. After 3 months of follow-up, these subjects’ study phase will be finished, at which time they will be offered the opportunity to start the self-help program if they so choose.

A second control condition pertains to the presence versus absence of a social presence. As described above, there will be two active control groups, one with and one without the eCoach Deborah in their version of the self-help tool.

#### Technical Specifications

CANreduce 2.0 is based on the content management system Drupal 7, with a MySQL database. It will be administered internally by the information technology (IT) developer at the institution where the principle investigator (PI) works as faculty. All access will be administered via encrypted and password-protected secure sockets layer connections to canreduce.ch [29]. At any time, any participant will have access to his or her own data only. The administrator will have full access to all of the data from all subjects.

All data will be entered online by the users themselves. The website ensures a certain degree of data validation, such as accepting only numbers for number fields, ensuring that users do not mark multiple choices for single choice questions, insisting that certain mandatory fields are filled out, and so on.

Module suggestion on the basis of open text answers for pros and cons for the keywords difficulty with falling asleep, tiredness, social inhibition, feelings of guilt, blaming oneself, and rumination.With social presence:Hello [participant’s user name]!You have been using the program for some time now and have already completed a few of the modules. Well done!If I may, I’d like to make a recommendation. I looked at your pros and cons of using cannabis and want to point out module 3 “Working on needs.“This module covers three important topics: better sleep, less rumination, and social contacts. Perhaps one of these topics will be particularly helpful in your current situation.Why don’t you have a look at it this evening?For questions or difficulties, feel free to contact me.Best regards,Your eCoach, DeborahWithout social presence:Hello,You have been using the program for some time now and have already completed a few of the modules. Well done!On the basis of your pros and cons of using cannabis, module 3 “Working on needs” would be recommendable.This module covers three important topics: better sleep, less rumination, and social contacts. Perhaps one of the topics would be particularly helpful in your current situation.Why don’t you have a look at it this evening?For questions, you can write to [contact].

**Table 4 table4:** Assessment instruments.

Assessment instruments	Initial assessment (t_0_)	Week 6 (t_1_)	3-month follow-up (t_2_)
Sociodemographics	X		
Center for Epidemiologic Studies Depression Scale	X		X
Short Screening Scale for DSM-IV^a^ posttraumatic stress disorder	X		X
General anxiety disorder-7	X		X
Adult ADHD^b^ Self-Report Scale-version 1.1	X		X
Quantity of cannabis use	X	X	X
Frequency of cannabis use	X	X	X
Cannabis Use Disorder Identification Test-Revised	X	X	X
Severity of Dependence Scale	X	X	X
Fragebogen Substanzanamnese	X	X	X
Client Satisfaction Questionnaire-I		X	
Intervention adherence^c^		X	
WAI-TECH^d^		X	
Negative effects according to Rozental			X

^a^DSM-IV: Diagnostic and Statistical Manual of Mental Disorders, 4th edition.

^b^ADHD: attention deficit hyperactivity disorder.

^c^Continuous assessment during 6 weeks.

^d^WAI-TECH: Working Alliance Inventory adapted for Web-based interventions.

CANreduce also features a responsive design and can automatically adapt to small screen devices such as tablets and mobile phones. Users can register online by choosing a username and providing a valid email address. To complete the registration process, users will have to click on a verification link sent to the email address specified, which will allow them to create a personal password, while preventing anyone from registering without a valid email address.

All data will be stored on a Web space hosted by an external provider that meets the IT security outsourcing regulations (99/2) of the Swiss Federal Banking Commission. Employees of the Web host will need to identify themselves with biometric data to gain physical access to the infrastructure.

Data will be extracted from the running Web-based database via Drupal and PHPmyAdmin. The data will then be stored at the PI’s institution on local computers for further processing and local file servers for archiving.

Each subject’s email address and phone number will be deleted after their participation in the study is complete and thereby, not available for either current or future analysis.

The investigator affirms and upholds the principle of every participant's right to privacy and that all personnel involved in the study will comply with applicable privacy laws. No individual data will ever be published or presented at scientific meetings.

### Measurements

Table 4 provides an overview of measurements. Sociodemographic data will include subject gender, age, and level of education.

The primary outcome of interest will be the number of days of cannabis use on the preceding 7 days according to the Time-Line-Follow-Back method [35,36].

Secondary outcomes of interest will include the quantity of cannabis used in the previous week, in standardized cannabis joints (as indicated in the consumption diary as well, as per Schaub et al [10]). Participants can choose between three different cannabis forms presented in photographs and in the second step between five different standard joints for each category (1/10 g, 1/6 g, 1/4 g, 1/3 g, and 1/2 g content pictures). These joints are either pure cannabis or cannabis mixed with tobacco. Finally, every participant has his or her personal standard tobacco cigarette, a ruler with centimeter and millimeter scales, the fraction amount in grams, and an open 10 cm paper prepared to roll a joint and containing the cannabis plant- or resin-tobacco mixture or pure cannabis presented in his or her consumption diary. Further secondary outcomes are the presence and severity of a cannabis use disorder (Cannabis Use Disorder Identification Test-Revised, CUDIT-R); the severity of cannabis dependence (Severity of Dependence Scale, SDS); the use of alcohol, tobacco, or other illicit drugs besides cannabis (Fragebogen Substanzanamnese, FDA); changes in depression, anxiety, and attention deficit symptoms (Center for Epidemiologic Studies Depression Scale, CES-D; general anxiety disorder-7, GAD-7; and Adult ADHD Self-Report Scale-V1.1, ASRS-V1.1); the Short Screening Scale for Diagnostic and Statistical Manual of Mental Disorders, 4th edition (DSM-IV) posttraumatic stress disorder (PTSD); client satisfaction (Client Satisfaction Questionnaire adapted to Internet-based interventions, CSQ-I); and treatment adherence. The perceived relationship between the user and the eCoach will be assessed at the end of the program using the Working Alliance Inventory [37] adapted for Web-based interventions (WAI-TECH).

The CUDIT-R is a questionnaire containing eight items designed to identify problematic cannabis consumption. Each item is a statement regarding cannabis use, to which respondents are provided with five response options, numbered from 0 to 4, that vary between questions, but for which increasing scores indicate increasing use or cannabis-related problems. As such, possible scores range from a minimum of 0 to a maximum of 32. A score of 8 or more indicates hazardous cannabis use, whereas a score of 12 or more indicates a possible cannabis use disorder [12].

The SDS is a reliable and valid 5-item screening scale, with a score of 4 or more being indicative of cannabis dependence [38].

The FDA asks about a person’s years of lifetime consumption, the past month’s consumption, and the manner of consumption for the DSM-IV or the International Statistical Classification of Diseases and Related Health Problems, 10th revision substances of abuse. This measure was derived from the EuropeASI, the European version of the Addiction Severity Index [39].

The CES-D Scale is a short self-report scale designed to measure depression symptoms in the general population [40]. All items on the scale are symptoms associated with depression that have been used in previously validated longer scales. CES-D responses rate the frequency at which depression symptoms have occurred over the past week. Possible scores on the CES-D-20 range between 0 and 60, where a CES-D-20 cutoff score of 16 is considered indicative of *significant* or *mild* depression symptoms. This is equivalent to experiencing six symptoms for most of the previous week or a majority of symptoms on 1 or 2 days. Higher scores indicate a higher symptom load.

The GAD-7 is a 7-item, self-report questionnaire to screen for and estimate the severity of GAD and has good reliability as well as factorial and concurrent validity [41]. These items ask about nervousness, inability to stop worrying, excessive worry, restlessness, difficulty relaxing, easy irritation, and the fear of something awful happening. Total scores range from 0 to 21, with a recommended cutoff score of 10 or higher.

The six-item short version of the ASRS-V1.1 can be self-administered easily and quickly [42]. With a total possible score of 24 and a cutoff score of 14, this six-item version has been shown to have strong concordance with clinician diagnoses, while significantly shorter than the full 18-item version.

The short screening scale for DSM-IV PTSD is designed to assess for a lifetime history of PTSD [43]. A score of 4 or more on the seven-symptom screening scale suggests PTSD.

The CSQ-I has been shown to be a suitable measure from the user’s perspective in the evaluation of Web-based health interventions. It is scored easily by summing up the individual item scores to produce a score ranging from 8 to 32, with higher scores indicating greater satisfaction [44].

Furthermore, the occurrence of any negative effects will be identified, as in Rozental et al, at the 3-month follow-up assessment [45].

Finally, we will ask all participants if they had used any other treatment than canreduce.ch during the 3 months and if so, to select from a predefined list of services.

As an indicator of treatment adherence, data will be collected on which modules have been completed by the participant and the number of weeks the consumption diary was filled out. Additionally, a script has been implemented that allows us to measure the time that subjects spend on each page. To avoid false data that might result if a participant leaves a Web page open but switches to a different window or leaves the computer, a cutoff time of 10 min inactivity has been set, after which the time spent on the page is disregarded and not saved to the database. These data could potentially lead to insights into how and specifically where to optimize CANreduce to further decrease attrition rates. We also will assess the number of individual emails received by each participant.

### Sample Size Calculation

Anticipating that a Cohen *d* of 0.30 based on our previous study experiences will be realistic for the effect size differences between the unenhanced version of the Web-based tool and the adherence-focused guidance-enhanced version, a sample size of n=176 in each study group would have 80% power to detect this difference based on calculations performed with G*Power software (Faul, Kiel) with an alpha error of 5% and two-tailed testing. Thus, we aim to recruit a total of 528 participants.

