### Hypotheses

We will test the following detailed study hypotheses with respect to the main outcome: reduction in the number of days of cannabis use over the past week, comparing the baseline, 6-week, and 3-month follow-up assessments:

An adherence-focused, guidance-enhanced, Web-based self-help program with a social presence (study arm 1) is more effective than an adherence-focused, guidance-enhanced, Web-based self-help program with no social presence (study arm 2) at reducing cannabis use.An adherence-focused, guidance-enhanced, Web-based self-help program to reduce cannabis use with a social presence (study arm 1) is more effective than TAU (study arm 3) at reducing cannabis use.An adherence-focused, guidance-enhanced, Web-based self-help program to reduce cannabis use without a social presence (study arm 2) is more effective than TAU (study arm 3) at reducing cannabis use.Participants in study arm 1 will demonstrate better adherence than participants in study arm 2 over the 6-week intervention.

We have similar expectations with respect to our secondary cannabis-related outcomes and will explore frequently co-occurring mental disorders as predictors of adherence and outcomes. Specifically, we also want to explore, for the first time, the influence of attention deficit hyperactivity disorder (ADHD) symptoms on adherence to and outcomes from a Web-based intervention among problematic cannabis users.

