### Limitations

The following protocol limitations must be considered:

First, cannabis users who are currently receiving other treatments to reduce their cannabis consumption will be excluded. However, CANreduce was designed to access cannabis users who—for personal or practical reasons—would not attend traditional addiction counseling. Second, all measurements will be self-reported. Third, most of the self-report instruments we will be using have not been validated in a Web-based context, though they have largely been validated in other research and clinical settings. Fourth, as found in the previous Web-based intervention [10,22], we expect rather high rates of dropouts. Finally, another possible limitation of Web-based studies is the potential for low adherence rate because of the distant nature of intervention.

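### The stated 80% power assumes complete follow-up and an effect size for a contrast that no pair of arms provides, so it is unsupported for the trial's hypotheses

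*Protocol article*

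**What the plan says.** The Sample Size Calculation section assumes a standardised difference of 0.30, which it attributes to the team's earlier work. It ties this figure to "the effect size differences between the unenhanced version of the Web-based tool and the adherence-focused guidance-enhanced version". From there it concludes that "a sample size of n=176 in each study group would have 80% power to detect this difference", "with an alpha error of 5% and two-tailed testing", and then: "Thus, we aim to recruit a total of 528 participants".

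The Limitations section, drawing on earlier web-based studies, says "we expect rather high rates of dropouts". It gives no rate.

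Study Design and Hypotheses define three arms: guidance-enhanced with social presence (arm 1), guidance-enhanced without it (arm 2), and treatment as usual (TAU) with access to the tool only after 3 months (arm 3). Hypothesis 1 is that arm 1 "is more effective than an adherence-focused, guidance-enhanced, Web-based self-help program with no social presence (study arm 2) at reducing cannabis use". Hypotheses 2 and 3 compare arms 1 and 2 with TAU.

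Data Analyses plans intention-to-treat mixed models with multiple imputation. The imputation model includes all primary and secondary outcomes.

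**The concern.** Two features of the sample size paragraph do not fit the rest of the article.

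- **No margin for loss.** The number to be recruited is the number that must be analysed, yet the same document expects many participants to be lost.
- **A contrast that is not in the trial.** The effect size is attached to a comparison with an unenhanced tool. Arms 1 and 2 both carry the adherence-focused guidance, and arm 3 receives no programme during the study period. Hypothesis 1 isolates social presence, which on the plain wording is only a component added on top of that guidance. No effect size is given for either comparison with TAU.

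The social-presence question is what the Discussion presents as new. A non-significant arm 1 versus arm 2 result would naturally be weighed against the advertised 80%, and that figure does not describe this comparison.

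**Working it through.** **Inputs from the Sample Size Calculation section:** d = 0.30, two-sided alpha 0.05, 176 per group, 528 in total. Randomisation is 1:1:1.

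**Assumed, because the article gives no figure:** follow-up loss of 20%, one third or 50%; a baseline-to-follow-up correlation of 0.5; d = 0.15 to 0.20 for social presence alone; d = 0.40 against TAU.

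**1. Reproducing the plan's figure.** For a two-sample t-test with n per arm, power comes from the noncentral t distribution with 2n − 2 degrees of freedom and noncentrality d × √(n/2).

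- Solving for 80% power at d = 0.30 gives n = 175.4, rounded up to 176.
- At n = 176, noncentrality = 0.30 × √88 = 2.81 and power = 80.1%.
- 3 × 176 = 528, so recruitment equals the complete-data requirement.

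**2. Effect of loss, per pairwise comparison at d = 0.30.** The number analysed per arm is 176 × (1 − loss). The adjusted column conditions on baseline, replacing d by d/√(1 − ρ²) = 0.30/√0.75 = 0.346.

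| Assumed loss | n per arm | Power, unadjusted | Detectable d at 80%, unadjusted | Power, baseline conditioned on, ρ = 0.5 |
|---|---|---|---|---|
| none | 176 | 80% | 0.30 | 90% |
| 20% | 140.8 | 71% | 0.34 | 83% |
| one third | 117.3 | 63% | 0.37 | 75% |
| 50% | 88 | 51% | 0.42 | 63% |

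**3. Effect of the contrast (unadjusted).**

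| Comparison | Assumed d | Power, complete data | Power, one-third loss |
|---|---|---|---|
| Arm 1 vs arm 2 | 0.15 | 29% | 21% |
| Arm 1 vs arm 2 | 0.20 | 46% | 33% |
| Active arm vs TAU | 0.40 | 96% | 86% |

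**4. Checking the contrast against the text.** The paragraph compares an unenhanced tool with a guidance-enhanced one. The Abstract, Study Design and Hypotheses call both active arms guidance-enhanced. The section on automated email feedback places adherence monitoring and feedback on demand in both arms, and the Social Presence section says that both get the same level of support. Taken literally, then, the pair behind d = 0.30 is neither arm 1 vs arm 2 nor either active arm vs TAU.

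**The case against.** **The calculation itself is correct.** This stands. The fault lies in the inputs, not in the arithmetic.

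**The loss figures describe a simpler analysis than the one planned.** This largely stands. They are for an unadjusted comparison of participants with data at one time point. The plan has mixed models over three assessments, and imputation can draw on week-6 cannabis outcomes for participants who gave them, so part of the lost information is recoverable. Conditioning on baseline could offset more, and at 20% loss with a correlation of 0.5 it would keep power above 80%. The gain depends on how the model is specified: a pure change score at that correlation gains nothing. The sample size paragraph claims no such gain, so the unadjusted figures are the conservative end of a range on the plan's own stated basis.

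**The loss rates have no source in the document.** Correct; they are illustrations. A reader might take the two-thirds completion reported for an Australian programme as a guide, but that is completion of another intervention, not follow-up retention here. The protocol also plans compensation, repeated reminders, a telephone interview and a fallback to the primary outcome only. These may hold loss down, but they do not put a margin into 528.

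**Unenhanced may be a loose label for arm 2.** This is possible, since the article calls the social-presence features enhancements specific to arm 1. On that reading 0.30 would be the hypothesis 1 effect, and the assumed 0.15 to 0.20 would carry less weight. The paragraph does not say so, however, and arm 2 is called guidance-enhanced elsewhere. Hypotheses 2 and 3 would still have no effect size, and the loss point would be untouched.

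**A stronger reading to avoid.** A reader might infer that the trial is underpowered for all its hypotheses. The document does not show that: against TAU no effect is given, and the true one may exceed 0.30. Nor does anything in it say that a non-significant result will be read as equivalence; that is a risk of interpretation, not a planned error.

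**Conclusion.** The 80% figure is a correct answer to a question that this trial does not ask.

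On its own t-test basis it holds only if nobody is lost, which the article does not expect. Power at d = 0.30 is then 71%, 63% and 51% at losses of 20%, one third and 50%. If baseline is conditioned on with a correlation of 0.5, it is about 83%, 75% and 63%. The loss rates and the correlation are assumptions.

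Separately, the effect size belongs to a contrast that no pair of arms provides as they are described, so power for hypotheses 1 to 3 is unsupported. It is most doubtful for arm 1 versus arm 2 and may well be adequate against TAU; both statements rest on assumed effects.

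The shortfall does not bias estimates or raise the false-positive rate. It affects what a non-significant result can be taken to mean.

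**What to change.** Keep 528 and rewrite the Sample Size Calculation paragraph:

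1. Name the contrast to which d = 0.30 applies. If unenhanced means arm 2, say so.
2. Give an effect size, with its basis, for each tested contrast: arm 1 vs arm 2, and each active arm vs TAU.
3. State an assumed follow-up loss and give power as a range. With one third and 50% as example rates, the text could read: *528 randomised gives about 117 (88) per arm with outcome data at one-third (50%) loss, i.e. 63% (51%) power at d = 0.30 unadjusted, and about 75% (63%) if baseline is conditioned on with a correlation of 0.5; the detectable d, unadjusted, is 0.37 (0.42).*
4. State that arm 1 vs arm 2 will be reported as an estimate with its confidence interval, and that non-significance will not be read as absence of a social-presence effect.

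The cost is one reworded paragraph and a less favourable stated power. No extra participants and no design change are needed.
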